### Allocation concealment and blinding

For ethical reasons, we decided against a double dummy design for blinding the patient, parents and care givers. Due to the differences in medication administration route and the significant nausea commonly associated with MTX blinding of the allocation to the patients, their families or their physicians is not possible. Where possible, however, blinding of an alternative clinician to score the wPCDAI, PCDAI and physician global assessment at each study visit should occur (prospective randomised open blind end-point (PROBE) evaluation).

### Safety

The external and independent advisory board of PIBDSETQuality serves as an independent data and safety monitoring board which meets at prespecified intervals with access to all data within the study. The principal investigator at each site is responsible for reporting any safety issues (adverse events, serious adverse events (SAEs), suspected unexpected serious adverse reactions), drop-outs or any new information which may impact the study in any way. The principal investigator shall report to the sponsor all SAEs experienced by a study subject receiving an ADA (Humira) within 24 hours of learning of the event regardless of the relationship of the event to the product. All SAEs are immediately sent to AbbVie pharmacovigilance by the sponsor. SAEs will be followed from the date of patient’s signature of informed consent, until complete resolution or 30 days after the end of the study/patient’s final study visit.

Participants may withdraw consent for further participation or data collection at any time without giving reason and without prejudicing further care or treatment. Patients will be permanently withdrawn from study treatment in the event of any of the situations outlined in box 5. Patients should be provided with a study alert card for use in the event of an emergency.

Box 5Criteria for premature termination of study treatment or participationPregnancy at any stage.Treatment failure as per protocol.Failure to tolerate allocated treatment or alternatives as listed within the protocol.Significant drug-related side effects manifesting as significantly abnormal bloods results or adverse effects based on the clinical judgement of the treating physician.Request of participant to be withdrawn from treatment.The judgement of the treating physician being that it is in the best interests of the participant to withdraw from study treatment.Loss of participant to follow-up.Patient death.

Biochemical markers are monitored with a clearly defined protocol for adjustments to therapy based on abnormal results (eg, neutropenia, pancreatitis, elevated liver enzymes).

### Data collection, management and monitoring

Patient CRFs are completed in a prospective manner using an electronic web-based system designed specifically by PIBDnet for this trial. In order to maintain data security and integrity, the web-based data entry will be linked to a password-secured Microsoft Access database, where data will be stored until time of analysis. Files will be saved on a code secured net-drive and backed-up following each data entry on a disk locked in a cabinet. Patients will be identified only by a study code assigned at the point of enrolment. Code of patient identifiers will be kept at each participating site. Handling of patient-identifiable is compliant with the legislation of each participating centre and the European General Data Protection Regulation. Investigators will be invited to fax or email the paper source document to the coordinating site on a random basis to allow appropriate monitoring. Access to data with detailed information on study outcomes will be made available to other research groups on request and at the discretion of the principal investigators.

Monitoring arrangements are in place for all sites after initial site initiation. The monitoring visits will occur regularly partly dependant on recruitment rate at individual sites. The monitoring is performed usually by someone external to the clinical team.

### Analysis and statistical methods

Descriptive statistics (mean, median, SD, SE, quartiles, minimum, maximum and two-sided 95% confidence limits of mean and median) will be presented for each treatment of the low and high-risk paediatric CD groups and where applicable, for the paired difference of each patient. Frequency tables will be presented where applicable.

### Primary analysis

Difference in the 12-month steroid/EEN free sustained remission rates between the treatment groups will be undertaken using X^2^ test. Mantel-Haenszel test will be used to combine data from all participating sites.

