Stratifying patients by risk for complex or severe CD may allow pre-emptive direction of maintenance strategy and potentially an early reduction in disease burden with subsequent improvement in long-term outcomes. The adult IBD Ahead initiative highlighted young age at diagnosis as a risk factor for severity of CD evolution^19^; all patients diagnosed within paediatric services would therefore be considered ‘high risk’. Paediatric consensus guidelines suggest that paediatric CD patients at ‘high risk for poor outcome’ should receive early therapy optimisation to modify progression of their disease.^1^ The guidelines list specific features which may be considered predictive for poor outcome in paediatric CD (see table 1).^1^ Patients deemed at high risk for complex disease or poor outcome may benefit from a ‘top-down’ approach as the TISKids (an RCT from disease diagnosis) aims to investigate.^20^

**Table 1 T1:** Definition of high-risk patients based on ECCO/ESPGHAN consensus guidelines

Defining high-risk Crohn’s disease patients	
ECCO/ESPGHAN consensus guidelines	Modified study criteria
Severe perianal disease	Complex perianal fistulising disease phenotype
Extensive (pan-enteric) disease; deep colonic ulcers on endoscopy	Panenteric disease phenotype (defined as L3 with L4b as per Paris classification^25^ or L3 with deep ulcers in the duodenum, stomach or oesophagus not related to non-steroidal anti-inflammatory medications or *Helicobacter pylori*)
	Overall cumulative disease extent of >/=60 cm
Stricturing and penetrating disease at onset	B2, B3 or B2B3 disease behaviour^20^
Marked growth retardation ≥2.5 height Z scores	Severe growth impairment (height z-score ≤2 or crossing ≥2 centiles) likely related to Crohn’s disease
Persistent severe disease despite adequate induction therapy	Hypoalbuminaemia (<30 g/L), elevated CRP (at least two times upper limit of normal range), or wPCDAI >12.5 despite at least 3 weeks of optimised induction therapy with steroids or EEN
Severe osteoporosis	Not included

CRP, C reactive protein; ECCO, European Crohn’s and Colitis Organisation; EEN, exclusive enteral nutrition; ESPGHAN, European Society for Paediatric Gastroenterology, Hepatology and Nutrition; wPCDAI, weighted Paediatric Crohn’s Disease Activity Index.

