### Secondary analyses

X^2^ tests or Fisher’s exact tests will be used to compare rates of remission, steroid intake, drop-out and SAEs between the two arms of each risk group and between the low and high-risk MTX groups. Logistic regression analyses may be performed to adjust for any imbalances in baseline covariates. To compare time to disease flare between the arms of each risk group and between high and low-risk MTX groups, a Kaplan-Meier survival estimate will be used and the log-rank test of equality over strata. A Cox proportional hazard model will be constructed to obtain a HR after validation of the proportionality assumption and adjusting for possible confounding variables (including age and disease duration). Student’s t tests or Wilcoxon rank sum tests will be used to compare growth, steroid dose, adverse events, changes in quality of life and patient reported outcomes between the two arms of each risk group and between the high and low-risk MTX groups. The predictive value of faecal calprotectin levels, CRP, serum tests or other clinical predictors for response (including genomic and serological markers) will be assessed for each arm of the study using sensitivity, specificity, negative and positive predictive values or area under the receiver operating characteristic curve. Multivariate logistic regression analyses will then be performed.

Analyses will be performed using the R software (http://cran.r-project.org). All comparisons will be made using a two-sided significance level of 0.05.

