#### Sample size considerations

Estimated remission rates are based on recent analysis from the RISK study,^18^ indicating an advantage of early anti-TNF introduction over immunomodulator therapy. For the low-risk group, it was hypothesised that 48% of children will be in remission at 12 months for the AZA/6MP arm versus 70% for the MTX arm. On the basis of this data with an alpha risk of 5% and a power of 80% a sample requirement of 88 patients per arm was calculated assuming a 10% lost to follow-up. For the high-risk group, it was hypothesised that 40% of children will be in remission at 12 months for the MTX arm versus 65% for the ADA arm. To detect this difference with an alpha risk of 5% and a power of 80%, a sample size of 68 participants is necessary, again assuming a 10% lost to follow-up. In total 312 participants will be included in the study (176 low-risk group; 136 high-risk group).

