### Discussion

REDUCE-RISK in CD is the first multicentre international RCT aiming to compare three different medication strategies for maintenance of remission in newly diagnosed CD based on a risk stratification protocol. During the 12-month follow-up period, the effects of the differing management strategies will be assessed via data collected and outcome measures as defined above in order to analyse the efficacy and safety of each medication and better define the most appropriate first-line maintenance immunomodulators to be used in specific subsets of CD patients. As a group we speculatively hypothesise that MTX will be superior to thiopurines for maintaining remission in CD in the low-risk group although in the absence of head to head studies prior to this one this study will provide randomised data to address this. Additionally, from our own work and others, we know response to induction therapy is an important prognostic marker and we wanted to allow the induction treatment to have a chance to work before we assigned high or low risk status.^23 24^ Thus, it was a pragmatic compromise with the timing of introduction of the maintenance treatment to give the induction treatment long enough to show its effect while recognising both treatments have a ‘lag period’ of a few weeks before they become fully effective.

We also hypothesise that ADA will be superior to MTX in the high-risk group based on the results from the RISK study.^18^ Of note ADA (Humira) was chosen to allow delivery of the study out of hospital, to reduce drug costs and it allowed single therapies to be compared with each other. Practically if we had used infliximab (Remicade) then we would have needed to use combination therapy which we did do not want to do as it would have further complicated the trial design.

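### The primary test uses no baseline wPCDAI or CRP within a risk group, and the only adjustment of remission rates is optional and tied to observed imbalance: a modest, cheaply recovered loss of efficiency

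*Protocol article*

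**What the plan says.** The Primary analysis section reads "Difference in the 12-month steroid/EEN free sustained remission rates between the treatment groups will be undertaken using" a chi-square test, and adds that the "Mantel-Haenszel test will be used to combine data from all participating sites". Site is the only factor named there.

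The only covariate adjustment of remission rates is under Secondary analyses: "Logistic regression analyses may be performed to adjust for any imbalances in baseline covariates". No covariates are listed, and no test or threshold for imbalance is given. The same section sets the error level: "All comparisons will be made using a two-sided significance level of 0.05".

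Four other places bear on the point:

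- Study end points builds the primary endpoint from wPCDAI and CRP at month 12, together with no relapse and no need for EEN or steroids since week 12.
- Table 1 (Introduction) uses wPCDAI and CRP after induction to assign risk. One route into the high-risk group is low albumin, raised CRP, "or wPCDAI >12.5 despite at least 3 weeks of optimised induction therapy with steroids or EEN".
- Randomisation and treatment allocation stratifies within each risk group by EEN or steroid induction only.
- The Discussion says "we know response to induction therapy is an important prognostic marker".

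**The concern.** wPCDAI and CRP at randomisation are early values of the quantities that make up the outcome. They are needed to allocate the risk group, and Box 3 lists both among the standard items for each study visit. If they predict sustained remission within a risk group, leaving them out of the comparison gives up precision that could be had without recruiting anyone.

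The adjustment rule that is stated does not recover it. In a randomised comparison, imbalance arises by chance. The gain from adjustment comes from how strongly a covariate predicts the outcome, whether or not the arms happen to differ on it. Choosing covariates by observed imbalance also leaves the adjusted result open to choice after the data are seen, in a trial where patients and treating physicians know the allocation.

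The stake is a few points of power in two comparisons that are each sized at about 80% for large differences (22 and 25 percentage points), plus the credibility of any adjusted analysis that is reported.

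**Working it through.** **Inputs from the document** (Sample size considerations). Low risk: "it was hypothesised that 48% of children will be in remission at 12 months for the AZA/6MP arm versus 70% for the MTX arm"; "with an alpha risk of 5% and a power of 80% a sample requirement of 88 patients per arm was calculated". High risk: 40% on MTX against 65% on ADA, 68 per arm (136 in total). Both allow 10% loss to follow-up. Alpha is 0.05 two-sided and allocation is 1:1.

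**Step 1: reproduce the stated sample sizes.** Pooled-variance formula without continuity correction, with p̄ the mean of p1 and p2:

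n = [1.960·√(2p̄(1−p̄)) + 0.842·√(p1(1−p1)+p2(1−p2))]² / (p2−p1)²

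- Low risk: p̄ = 0.59, and the two roots are 0.6956 and 0.6779. n = (1.3633 + 0.5706)²/0.0484 = 77.3, so 78 evaluable; 78/0.9 = 86.7, so 87 against 88 stated.
- High risk: p̄ = 0.525, and the two roots are 0.7062 and 0.6837. n = (1.3842 + 0.5754)²/0.0625 = 61.4, so 62 evaluable; 62/0.9 = 68.9, so 69 against 68 stated.

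Both agree within one patient per arm. The plan's 80% therefore rests on an unadjusted two-proportion test.

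**Step 2: power of the unadjusted test.** Evaluable n per arm is 88 × 0.9 = 79 and 68 × 0.9 = 61.

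Power = Φ{[(p2−p1)√n − 1.960·√(2p̄(1−p̄))] / √(p1(1−p1)+p2(1−p2))}

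- Low risk: Φ[(0.22 × 8.888 − 1.3633)/0.6779] = Φ(0.873) = 80.9%.
- High risk: Φ[(0.25 × 7.810 − 1.3842)/0.6837] = Φ(0.831) = 79.7%.

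**Step 3: power with prespecified adjustment.** If the covariates explain a share R² of the outcome variance within a risk group, the effective n is n/(1−R²). The document gives no R². The range 0 to 0.20 is an assumption, equivalent to an odds ratio of 1 to 3 per SD of a prognostic score.

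| Assumed R² | Low risk | High risk |
|---|---|---|
| 0 | 80.9% | 79.7% |
| 0.05 | 82.9% | 81.7% |
| 0.10 | 84.8% | 83.8% |
| 0.20 | 88.8% | 87.9% |

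Example, low risk at 0.10: 79/0.9 = 87.8 and √87.8 = 9.369, so Φ[(0.22 × 9.369 − 1.3633)/0.6779] = Φ(1.029) = 84.8%. At R² = 0.10, the evaluable number per arm needed for 80% power falls from 78 to 71 (low risk) and from 62 to 56 (high risk).

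**Step 4: simulation check.** 6,000 trials per cell, chi-square against covariate-adjusted logistic regression (Wald test).

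| R² (approx.) | Low risk | High risk |
|---|---|---|
| 0 | 81.2% → 81.3% | 81.9% → 80.2% |
| 0.10 | 80.7% → 84.6% | 81.1% → 83.3% |
| 0.20 | 79.3% → 87.6% | 80.8% → 86.4% |

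The Monte Carlo standard error of each figure is about √(0.8 × 0.2/6000) = 0.5 points. The formula is borne out, with slightly smaller gains in the high-risk group and a cost of 81.9 − 80.2 = 1.7 points there when the covariates carry no information.

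**Step 5: where the gain is plausible.** By Table 1, a child with wPCDAI above 12.5 or CRP at least twice the upper limit after at least 3 weeks of induction is high risk. Low-risk children assessed after that time therefore have wPCDAI of at most 12.5 and CRP below twice the limit. The restriction is not complete: the endpoint's CRP limit is 1.5 times, and inclusion at week 5±3 starts at week 2, before the 3-week criterion can apply. The high-risk group mixes children who enter on phenotype, some possibly already at remission level, with children who failed induction. Prognosis may well differ more there.

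**The case against.** The strongest reply is that nothing in the primary test is wrong. In a randomised comparison an unadjusted chi-square is valid, it is the basis on which the trial was sized, and it has the planned power. The design also already uses wPCDAI and CRP, because they help to split patients into the risk groups within which arms are compared. The Discussion sentence on induction response explains the timing of that split and gives no strength of association within a group. All of this stands, and it limits the point to efficiency.

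A further reply is that this is an article and that covariate lists belong in an analysis plan that is not shown. That carries less weight. The article is not silent: it states an unadjusted primary test and states a basis for adjustment, and that basis is poor.

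Two stronger readings are tempting. First, a reader might assume a correlation of 0.5 between baseline status and outcome (R² = 0.25) and infer that power of about 90% is being given up. No figure in the document supports 0.5, and the endpoint also counts relapse and steroid or EEN use. Range restriction works against it too. As an illustration, assume a normal covariate with correlation 0.5 over all patients and the low-risk group as the better 50% to 60%. The within-group correlation is then about 0.33 to 0.35, and low-risk power about 85% to 86%. Second, a reader might simulate adjustment that fires only when an imbalance test gives p < 0.05. The document contains no such test or threshold, so figures from that exercise do not describe this plan.

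**Conclusion.** The concern holds in limited form. The primary comparison is valid, unbiased and powered as planned, but it ignores baseline wPCDAI and CRP within each risk group. The only adjustment of remission rates is optional, without named covariates, and triggered by imbalance instead of prognostic strength.

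The size depends on an R² that the document does not give. Over 0 to 0.20, power would be about 81% to 89% in the low-risk group and 80% to 88% in the high-risk group. At 0.05 to 0.10 the gain is about 2 to 4 points. It is likely to be smaller in the low-risk group (176 of 312 patients) and more plausible in the high-risk group. Nothing here supports a claim that the trial is underpowered or its primary result biased. Even if the gain in power proves small, a fixed covariate list is better than one chosen after the data are seen.

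**What to change.** Before database lock, prespecify one covariate-adjusted primary analysis in each risk group:

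- Logistic regression of sustained remission on arm, wPCDAI at randomisation, log CRP at randomisation, and the EEN/steroid randomisation stratum.
- Report the standardised (marginal) risk difference with its 95% confidence interval, so that the result stays on the scale of the sample-size assumption.
- State how site is handled, since the current text combines sites by Mantel-Haenszel.
- Keep the chi-square/Mantel-Haenszel result as supportive.
- Set a rule for missing baseline CRP.
- Replace the sentence "Logistic regression analyses may be performed to adjust for any imbalances in baseline covariates" with this fixed covariate list.

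The cost is analysis wording only, with no added patients, visits or measurements. The downside is a few extra parameters in models with about 60 to 80 evaluable children per arm, and a possible loss of up to about 2 points of power in the high-risk group if the covariates turn out to carry no information.

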### Secondary analyses

X^2^ tests or Fisher’s exact tests will be used to compare rates of remission, steroid intake, drop-out and SAEs between the two arms of each risk group and between the low and high-risk MTX groups. Logistic regression analyses may be performed to adjust for any imbalances in baseline covariates. To compare time to disease flare between the arms of each risk group and between high and low-risk MTX groups, a Kaplan-Meier survival estimate will be used and the log-rank test of equality over strata. A Cox proportional hazard model will be constructed to obtain a HR after validation of the proportionality assumption and adjusting for possible confounding variables (including age and disease duration). Student’s t tests or Wilcoxon rank sum tests will be used to compare growth, steroid dose, adverse events, changes in quality of life and patient reported outcomes between the two arms of each risk group and between the high and low-risk MTX groups. The predictive value of faecal calprotectin levels, CRP, serum tests or other clinical predictors for response (including genomic and serological markers) will be assessed for each arm of the study using sensitivity, specificity, negative and positive predictive values or area under the receiver operating characteristic curve. Multivariate logistic regression analyses will then be performed.

Analyses will be performed using the R software (http://cran.r-project.org). All comparisons will be made using a two-sided significance level of 0.05.

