Box 1Study endpointsPrimary endpointSustained steroid/exclusive enteral nutrition (EEN)-free remission at month 12, where sustained remission is defined as weighted Paediatric Crohn’s Disease Activity Index (wPCDAI) ≤12.5 and C reactive protein (CRP) ≤1.5 times the upper limit without a relapse or need for EEN/steroids since week 12.Secondary endpointsComparing the following within (1) the two treatment arms per risk group; (2) methotrexate treatment between high and low-risk groups and (3) tOP-down adalimumab (high-risk group) versus step-pp adalimumab (ancillary study):Rate of clinical remission at month 12 (physician global assessment, wPCDAI, PCDAI).Relapse free remission with normal CRP at month 12.Relapse-free remission with normal CRP and faecal calprotectin <300 at month 12.Remission at week 12 (measured by wPCDAI≤12.5 and normal CRP and being off steroids/EEN).Time to first relapse after week 12.Predictive value of faecal calprotectin values at visits 1, 2, 4 and 6 (respectively at month 0, 2, 6 and 12).Drop-out rates.Adverse drug event rate including pharmacogenomics for toxicity and response to therapy.Height velocity and z-score at baseline and 52 weeks.Quality of life as measured by the IMPACT 3 questionnaire completed at each study visit.Health economic evaluation at all visits (forms EQ-5D-Y proxy 1, EQ-5D-Y and EQ-5D-5L, Productivity and Activity Impairment Questionnaire (WPAI):Crohn’s disease Caregiver, School Attendance start of the research and follow-up visits).

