### Eligibility criteria and recruitment

Full eligibility criteria for the study are listed in box 2. Patients are eligible if aged 6–17 years with new-onset (<6 months) treatment naïve luminally active and/or perianal fistulising CD diagnosed as per revised Porto criteria^21^ receiving steroids or EEN for induction of remission with wPCDAI >40 or CRP >2 times upper limit of normal at diagnosis. Eligible definitions of disease behaviour were derived from the Paris classification.^22^ Informed consent from must be obtained prior to participation in the study. Patients are excluded in cases of previous use of IBD-related medications, pregnancy or refusal to use contraceptives; disease requiring surgery, contraindications to study medication, exposure to live vaccine within 3 weeks, oral anticoagulant or antimalarial use, current or previous malignancy, significant infection or significant comorbidity.

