##### Induction therapy

All enrolled patients receive either corticosteroids or EEN as induction as determined by the clinical team and the patient/caregiver. For EEN any balanced formula (polymeric or elemental) administered orally or via nasogastric tube is permitted and should be prescribed for 6–8 weeks. Tapering of steroids is at the discretion of the prescribing clinician. Adaptation of induction therapy (eg, dose increase of steroids or return to EEN) or crossover from one induction therapy to the other is permitted in order to achieve remission, however, patients must have discontinued their induction therapy by week 12. If induction therapy is not discontinued by week 12, the patient is considered a treatment failure, with the protocol for this detailed below.

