### Randomisation and treatment allocation

Randomisation is undertaken following allocation to high or low-risk group at week 5±3 weeks. This process uses an integrated module within the electronic case report form (CRF) system. Within both the high and low-risk groups patients are 1:1 randomised to MTX vs ADA or AZA/6MP, respectively, in blocks of four stratified by EEN or steroid induction therapy. Code for randomisation is prepared and held by the central coordinating site and site coordinators are then informed of the results. Immunomodulator or biological therapy should be commenced within 2 weeks of randomisation as per the protocol outlined in table 2.

**Table 2 T2:** Medication protocol for low and high-risk patients following randomisation

	Therapy	Route	Dose	Notes
Low risk protocol	Methotrexate	SC	15 mg/m^2^ body surface area weekly (max dose 25 mg).	Ondansetron 4–8 mg orally 1-hour preinjection and folic acid 15 mg (5 mg in patients <20 kg) 3 days postinjection are recommended for all patients.

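### The time-to-relapse analysis does not name induction therapy, the factor that stratifies randomisation; stratifying by it is a small gain at almost no cost

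*Protocol article*

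**What the plan says.** In the Protocol article, Randomisation and treatment allocation, patients in each risk group are randomised 1:1 "in blocks of four stratified by EEN or steroid induction therapy". The type of induction is not itself randomised. Under Induction therapy: "All enrolled patients receive either corticosteroids or EEN as induction as determined by the clinical team and the patient/caregiver".

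The endpoint concerned is a secondary one, listed in Box 1: "Time to first relapse after week 12". Under Secondary analyses, "a Kaplan-Meier survival estimate will be used and the log-rank test of equality over strata". A Cox model follows, "adjusting for possible confounding variables (including age and disease duration"; the word *including* leaves the list open. The same methods are used for the two arms within each risk group and for methotrexate patients in the high-risk against the low-risk group.

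Induction therapy is not named as a stratum or covariate in the Primary or Secondary analyses sections. The only stratifying variable they name is site, in the Mantel-Haenszel test for the primary endpoint.

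**The concern.** Stratified randomisation balances the arms on the stratification factor. If that factor also predicts relapse, the treatment contrast varies less from trial to trial than an unstratified log-rank test assumes. The test then rejects less often than its nominal level and can lose power. Analysing by the strata used for randomisation corrects this.

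The article names two example covariates but not the variable that the design itself treats as important. The phrase "the log-rank test of equality over strata" does not settle the matter. Strata there could mean the treatment arms being compared, as in some software output, or a test stratified by some factor. Two analysts could carry out the sentence differently. At stake is a little efficiency and some clarity on a secondary endpoint.

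**Working it through.** **Inputs from the Protocol article (Sample size considerations; Secondary analyses).** Low risk: 48% v 70% in remission at 12 months, 88 per arm. High risk: 40% v 65%, 68 per arm. Two-sided alpha 5%, power 80%, 10% lost to follow-up. No event count, hazard ratio or power is given for time to relapse.

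**Step 1. Reproduce the stated sizes.** n per arm = [1.96·√(2p̄(1−p̄)) + 0.8416·√(p₁(1−p₁)+p₂(1−p₂))]² / (p₁−p₂)².
- Low risk: p̄ = 0.59; (1.363 + 0.571)² / 0.0484 = 77.3, so 78; 78/0.9 = 86.7, so 87 (stated 88).
- High risk: p̄ = 0.525; (1.384 + 0.575)² / 0.0625 = 61.4, so 62; 62/0.9 = 68.9, so 69 (stated 68).

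Both agree to within one patient per arm, so the stated rates are a sound basis for calibration.

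**Step 2. Translate to time to relapse.** Assume that every non-remission is a relapse and that hazards are proportional. After 10% loss, 79 and 61 per arm remain (0.9 × 88 = 79.2; 0.9 × 68 = 61.2).
- Low risk: HR = ln 0.70 / ln 0.48 = 0.49; events = 79 × (0.52 + 0.30) = 64.8; Schoenfeld power = Φ(½√64.8·|ln HR| − 1.96) = 83%.
- High risk: HR = ln 0.65 / ln 0.40 = 0.47; events = 61 × (0.60 + 0.35) = 58.0; power 82%.

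**Step 3. Compare the two tests by simulation.** There were 8000 runs per setting, with blocks of four within two induction strata and exponential relapse times. For stratum share π and stratum hazard ratio θ, each arm's hazard h solves (1−π)e^(−h) + πe^(−hθ) = stated remission rate, so the 12-month rates stay fixed as θ changes. The values of θ and π are assumptions; the article gives neither. Results for π = 50% (unstratified → stratified):

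| θ | Low-risk power | High-risk power | Low-risk type I error | High-risk type I error |
|---|---|---|---|---|
| 1 | 82.0 → 81.8% | 80.7 → 80.7% | 5.6 → 5.5% | 4.8 → 4.7% |
| 1.25 | 81.7 → 81.9% | 81.7 → 81.9% | 5.0 → 5.1% | 4.8 → 4.9% |
| 1.5 | 82.8 → 83.3% | 81.5 → 82.3% | 4.8 → 4.9% | 4.9 → 5.2% |
| 2 | 82.3 → 83.5% | 81.9 → 83.9% | 4.3 → 5.1% | 3.8 → 4.7% |
| 3 | 84.4 → 87.8% | 83.5 → 87.9% | 3.3 → 5.0% | 3.3 → 5.0% |

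The comparison should be made within a row, because the treatment hazard ratio within strata shifts slightly with θ to keep the 12-month rates fixed. The Monte Carlo standard error of one power figure is √(0.82 × 0.18 / 8000) = 0.4 points, but both tests were run on the same data sets. With π = 25% the picture is similar. At θ = 3 power is 83.7 → 87.4% (low risk) and 82.8 → 87.1% (high risk), with unstratified type I error of 3.4% and 3.7%.

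**The case against.** The strongest reply is that the article has not left the factor out. The covariate list is open and *strata* is undefined, so a stratified test may be what is meant. An article also commonly leaves final covariate lists to the full protocol or analysis plan. This stands as far as it goes: the supportable statement is that the factor is not named, not that it is excluded. But the article does state the test and give example covariates, and one phrase would remove the ambiguity.

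Second, nothing in the article says that EEN versus steroids predicts relapse. A reader might infer it from the Discussion, which calls response to induction prognostic. That is response, not type, and poor response already places a patient in the high-risk group (Table 1), so it is largely absorbed before randomisation. This also stands, and it is why the stratum effect is treated as unknown. The counterweight is that stratifying costs essentially nothing when the effect is nil.

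Third, a reader might infer that naming disease duration wastes power, since eligibility requires "Patients are eligible if aged 6–17 years with new-onset (<6 months) treatment naïve luminally active" disease. One weak covariate costs almost nothing. The same methods serve the high- versus low-risk methotrexate comparison, which is not randomised and where adjustment for confounders is appropriate. The criticism of that covariate does not hold.

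**Conclusion.** The point holds as a minor, almost free improvement. Randomisation is stratified by induction therapy, and the time-to-relapse analysis does not name it. Stratifying gains about 0 to 1 point of power for a stratum hazard ratio up to 1.5, 1 to 2 points at 2, and 3 to 4 points at 3. At 3 the unstratified test's type I error is about 3.3 to 3.7% across the two splits examined. The error is in the conservative direction, so false positives are not inflated.

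These sizes rest on assumed stratum hazard ratios and splits, exponential times, and treating every non-remission as a relapse. Splits more extreme than 25:75 were not examined.

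Two stronger readings are not supported. One is that ignoring the stratum leaves the endpoint underpowered: unstratified power stays above 80% in every setting run, and the article sets no power target for this endpoint. The other is that obtaining the hazard ratio only "after validation of the proportionality assumption" could leave the endpoint with no result: the Kaplan-Meier estimates and log-rank test remain, and a fallback summary measure is detail commonly left to the analysis plan.

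**What to change.** For the two comparisons within risk group, state that the log-rank test and the Cox model are stratified by induction therapy (EEN or steroids) as recorded at randomisation, and let this replace the undefined strata. The value used by the randomisation module should be kept even if a patient later crosses over, since the Induction therapy section allows crossover. Age and disease duration may stay as covariates, including for the non-randomised high- versus low-risk methotrexate comparison, where this stratification is not required by the randomisation.

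The cost is one sentence of analysis wording. The stratum is already recorded, so no new data or patients are needed, and if induction type is not prognostic the loss of power is negligible (82.0 v 81.8% in low risk, 80.7 v 80.7% in high risk).
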